## Randomisation

Participants will be randomised to receive telmisartan 20, 40, 80 or control (no intervention) in a 1:1:1:1 ratio once (A) eligibility criteria have been fulfilled; (B) fully informed written consent has been obtained; and (C) baseline assessments have been completed. Participants will be randomised using a bespoke secure (24 h) web based randomisation programme controlled centrally by the CTRC, University of Liverpool. For each recruiting centre, randomisation will be stratified by ethnicity (African-American and non-African-American) where ethnicity is determined by self-categorisation using the NHS ethnicity codes. Centres will be provided with emergency back-up randomisation envelopes to be used in the event of a system failure or when a system failure cannot be resolved in a reasonable time frame. Patients may only be randomised into the study by an authorised member of staff at the study site as detailed on the delegation log. Participants may only be randomised into the study once.

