## Outcomes and assessments

Efficacy of trial treatments will be assessed throughout the period of the study. The primary outcome measure is a reduction in insulin resistance (as measured by HOMA-IR) in telmisartan treated arm(s) after 24 weeks of treatment in comparison with the non-intervention arm. Fasting plasma and serum samples will be collected from each participant at baseline and at follow-up visits (weeks 12, 24 and 48) and stored under appropriate conditions locally. Biochemical analyses will be carried out centrally in an accredited clinical laboratory. Fasting plasma glucose will be measured by standard clinical methods and serum insulin will be measured by an electrochemiluminescence immunoassay using a Cobas C Analyser (Roche Diagnostics, Switzerland). HOMA-IR will be calculated using the equation: (fasting serum insulin (mU/L)×fasting plasma glucose (mmol/L))/22.5. The secondary outcome measures are detailed in box 2. Serum and urine biomarker analyses and DNA extraction will be performed centrally using Human Multiplex ELISA (Millipore) on a BioPlex 200 System (BioRad) and Chemagic Magnetic Separation Module I (MSM I), respectively.
Box 2Secondary outcome measuresChange in lipid profile (total cholesterol, triglycerides, LDL-c and HDL-c) at weeks 12, 24 and 48 between telmisartan treated arm(s) and the control arm.Change in body fat redistribution as measured by MRI/MRS at 24 weeks between telmisartan treated arm(s) and control arm (See substudy).Change in plasma concentrations of biomarkers (adiponectin, lipin1, IL-6, TNF-α, resistin and hs-CRP) at 12, 24 and 48 weeks between telmisartan treated arm(s) and control arm.Change in insulin resistance, measured longitudinally at weeks 12 and 48, in telmisartan treated arm(s) in comparison with the control arm.Change in urinary biomarker levels at 12, 24 and 48 weeks between telmisartan treated arm(s) and the control arm.Difference in expected and unexpected serious adverse events between different telmisartan treated dose arm(s) and the control arm over the study follow-up.HDL-c, high density lipoprotein-cholesterol; hs-CRP, high sensitive, C reactive protein; IL-6, interleukin-6; LDL-c, low density lipoprotein-cholesterol; TNF-α, tumour necrosis factor-α.

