## Sample size calculation

The primary response from each patient is the difference between the baseline HOMA-IR score and their HOMA-IR score at 24 weeks. The design has been constructed under the assumption that for all patients this response is normally distributed with a common SD, σ.

The sample size calculation is based on a one-sided type I error of 5% and a power of 90%. If there is no difference between the mean response on any treatment and that on control, then a probability of 0.05 is set for the risk of erroneously ending the study with a recommendation that any treatment be tested further. For the power, we adopt a generalisation of this power requirement to multiple active treatments due to Dunnett.^40^ Effect sizes are specified as the percentage chance of a patient on active treatment achieving a greater reduction in HOMA-IR score than a patient on control as this specification does not require knowledge of the common SD, σ. The requirement is that, if a patient on the best active dose has a 65% chance of a better response than a patient on control, while patients on the other two active treatments have a 55% chance of showing a better response than a patient on control, then the best active dose should be recommended for further testing with probability 1−β=0.90. A 55% chance of achieving a better response on active dose relative to control corresponds to a reduction in mean HOMA-IR score of about a sixth of an SD (0.178σ), while the clinically relevant effect of 65% corresponds to a reduction of about half an SD (0.545σ). The critical values for recommending that a treatment is taken to further testing at the interim and final analyses (2.782 and 2.086) have been chosen to guarantee these properties using a method described by Magirr *et al*,^41^ generalising the approach of Whitehead and Jaki.^42^

The maximum sample size of this study is 336 evaluable patients, although the use of the interim analysis may change the required sample size. The study will recruit additional patients to account for an anticipated 10% dropout rate.

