## Statistical analysis

### Primary outcome analysis

Three different doses of the intervention will be evaluated against the control in stage 1 of the study and an interim analysis will take place that will allow ineffective doses to be eliminated quickly while a dose showing a positive effect can be taken forward. An ANCOVA model will be fitted for a 24 week HOMA-IR score adjusting for the stratification factor (African-American and non-African-American), and the corresponding t—values will be used to construct test statistics expressing the advantage of each of the active treatments over control. The largest of these test statistics will be compared to the interim critical value (2.782) and proceed as discussed above at the interim analysis. At the final analysis, if the largest comparative test statistic exceeds the final critical value (2.086), then this dose would be recommended for further study. Adjustments can be made to allow for any discrepancies between target and actual sample sizes while still preserving the one-sided type I error rate at 0.05.

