## Time frame and trial status

TAILoR is currently recruiting from 19 specialist HIV centres throughout the UK. The study has so far recruited 293 patients and has been given a no-cost extension to continue recruitment till the end of July 2015. Each participant is followed up for a total of 48 months. The total study period is 56 months.

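### Randomisation is stratified by centre and ethnicity but the primary ANCOVA adjusts for ethnicity only, which makes the test mildly conservative if the outcome differs between centres

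*Protocol article*

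**What the plan says.** The Randomisation section of the protocol article states: "For each recruiting centre, randomisation will be stratified by ethnicity". On a plain reading, allocation is balanced separately in each centre-by-ethnicity cell. The Time frame and trial status section gives the number of centres: "TAILoR is currently recruiting from 19 specialist HIV centres throughout the UK".

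The Primary outcome analysis section then fixes the model as an ANCOVA for 24-week HOMA-IR, "adjusting for the stratification factor (African-American and non-African-American". The factor is singular and is defined as ethnicity. The t-values from this model are the statistics compared with 2.782 at the interim and 2.086 at the end. Nowhere does the article enter centre in the primary model or explain why it is left out.

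**The concern.** Balancing the arms within centre removes differences between centres from the true sampling variance of each dose-versus-control contrast. A model without centre leaves those differences in the residual, so the reported standard error exceeds the true one. The t-values are then too small, and the actual type I error falls below the 0.05 for which the boundaries were chosen. Part of the precision gained by randomising within centre is not used. The same t-values drive both the interim decision (stop, drop a dose or continue) and the final recommendation.

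All of this depends on the outcome differing between centres. If it does not, nothing is lost.

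**Working it through.** **Inputs from the protocol article.** 1:1:1:1 allocation; 42 patients per arm at the interim and 84 at the end (336/4); critical values 2.782 and 2.086; doses with a negative interim statistic dropped; one-sided error 0.05; power 0.90; effects 0.545 SD for the best dose and 0.178 SD for the other two; 19 centres and 2 ethnicity levels.

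**Assumed, because the article does not give them.** Between-centre share of outcome variance (ρ) from 0 to 0.20; permuted blocks of 4 (or 8) within each cell; 25% of patients in one ethnic group; equal (or skewed) centre sizes; total SD of 1.

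**Step 1: reproduce the stated design.** The effects are √2 × z(0.65) = 0.545 and √2 × z(0.55) = 0.178. In 2,000,000 simulated trials with 42 per arm per stage, the familywise error is 0.0501 and the power to select the best dose is 0.906. With 41 per arm per stage the power is 0.8998. The plan's figures hold.

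**Step 2: the mechanism.** With perfect balance within centres, the true variance of a contrast is (1 − ρ) × 2σ²/n. The model without centre estimates about 2σ²/n, so the standard error is overstated by the factor 1/√(1 − ρ). At n = 84 and σ = 1 the model reports √(2/84) = 0.154, while at ρ = 0.10 the true value is √(0.9 × 2/84) = 0.146. This factor is an upper limit, because 19 × 2 = 38 cells hold on average only 336/38 ≈ 9 evaluable patients and many blocks stay incomplete.

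**Step 3: simulation with incomplete blocks.** There were 40,000 trials per scenario, with equal centres and blocks of 4, analysed by least squares with and without fixed centre effects. A familywise error is counted when any dose is recommended under the null.

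| ρ | Upper limit 1/√(1 − ρ) | Model SE / true SD, ethnicity only | Familywise error: ethnicity only | Familywise error: plus centre | Power: ethnicity only | Power: plus centre |
|---|---|---|---|---|---|---|
| 0 | 1.000 | 1.003 | 0.051 | 0.052 | 0.907 | 0.905 |
| 0.05 | 1.026 | 1.017 | 0.046 | 0.052 | 0.909 | 0.913 |
| 0.10 | 1.054 | 1.051 | 0.041 | 0.052 | 0.920 | 0.929 |
| 0.20 | 1.118 | 1.097 | 0.032 | 0.051 | 0.932 | 0.950 |

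Power is the probability of selecting the best dose. With centre in the model, the SE ratio is 1.00 throughout. The simulation error of an error rate near 0.05 is √(0.05 × 0.95/40,000) ≈ 0.001. Both models were fitted to the same simulated data, so the differences in power are more precise than the individual values.

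**Step 4: sensitivity at ρ = 0.10.** Blocks of 8 give a familywise error of 0.042, and skewed centre sizes give 0.043. The direction does not change.

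**Step 5: random intercept.** A further simulation with a random intercept for centre in place of fixed effects also brought the error back to about 0.05. The gain was about 0.3 to 0.9 points of power for ρ of 0.05 to 0.10, with no loss at ρ = 0.

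**The case against.** The strongest reply is that the stated model does no harm. It never inflates type I error, and power for the best dose is at or above 0.90 in every scenario. With ethnicity only, power even rises with ρ, from 0.907 to 0.932, because balance within centres shrinks the true variance while the total SD stays fixed. This stands. A reader might infer that the trial becomes underpowered or that its error control fails; the article's figures support neither. The loss is relative to a better model, not to the planned 90%.

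Second, the driving quantity is unknown and may be small. The Outcomes and assessments section has samples "stored under appropriate conditions locally", from which one might infer centre effects. The same section has the assays run centrally, which removes differences between laboratories. The sample size section also defines the response as change from baseline. If baseline is subtracted or adjusted for, stable centre differences in HOMA-IR level largely drop out, and the relevant ρ is that of what remains. This also stands, and is why a range that includes zero is shown.

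Third, the formula for perfect balance overstates the effect. It would give errors of 0.044 and 0.038 at ρ of 0.05 and 0.10, where incomplete blocks give 0.046 and 0.041. The latter are used here.

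Fourth, a condensed article may leave the handling of centre to the analysis plan. This carries less weight: the article is not silent on covariates but names the model and defines its single adjustment factor, which does not match its own account of the randomisation.

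**Conclusion.** The point holds as a modest mismatch between randomisation and analysis. Centre is a randomisation factor and the primary model omits it. For an assumed between-centre share of 0%, 5% and 10%, the standard error is overstated by about 0%, 2% and 5%, and the one-sided familywise error is about 0.05, 0.046 and 0.041. The forgone power is about 0.4 points at 5% and 0.9 points at 10%.

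The validity of the trial is not in question. The sizes rest on the assumed ρ, on blocked allocation within centre-by-ethnicity cells and on normally distributed outcomes. If centres do not differ after any baseline adjustment, the effect is nil.

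**What to change.** In the Primary outcome analysis section, name both randomisation factors: ethnicity as a fixed effect, and centre either as a random intercept or as a fixed effect with small centres pooled by a rule set in advance. State that the same model supplies the test statistics at the interim and final analyses. If centre is to stay out, give the reason.

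The cost is a change of wording made before the data are analysed. Centre is known from the randomisation itself. If centres turn out not to differ, fixed centre effects cost about 0.2 points of power (0.907 against 0.905), and the random intercept showed no loss. Whether to adjust for baseline HOMA-IR is a separate question, and this change does not depend on it.

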## Trial interventions

Telmisartan is an angiotensin receptor antagonist indicated for clinical use as an antihypertensive agent. It is also used to reduce cardiovascular events in patients who are at risk. However, the current trial uses telmisartan outside its licensed indications.

At the onset of the trial, telmisartan was under patent (Boehringer Ingelheim GmBH; Micardis); however, during the course of the trial, the patent expired and several manufacturers started marketing generic telmisartan, which was then also used in the trial, but the trial will continue to use Micardis SPC as the reference SPC. Telmisartan used in this trial is sourced via usual local NHS procurement arrangements.

Telmisartan tablets are available in 20, 40 or 80 mg doses and therefore fit in with the dose range to be used in the trial prior to interim analysis. In most cases, the participant is provided their required dose in one tablet. Telmisartan tablets are for once-daily oral administration and should be taken with liquid, with or without food. The CRFs will be used to record which brand has been dispensed to the participant. Telmisartan is stored as per the manufacturer's SPC.

For each randomised patient, treatment is for a maximum period of 48 weeks. The principal investigator or delegated other will issue a prescription based on the patient's randomisation status and the trial treatment can start immediately after randomisation. For the three treatment arms, treatments will be dispensed at the appropriate doses at baseline, at 12 weeks and then at 24 weeks, unless interruption or discontinuation is warranted. Wherever titration of dose is required, the treatment starts with 20 mg and is then titrated upwards over a period of 2 weeks (for a 40 mg dose) or 4 weeks (for an 80 mg dose). At 48 weeks, administration of trial treatments will be stopped and any unused medications will be returned to pharmacy for disposal via their local procedures. There is a 2 week attendance window on either side of each of the follow-up visits and a 4 day window on either side of the titration visits.

Since the results of the interim analysis decide the design of stage II of the trial, those patients who are on a dose that is not taken forward to stage II will be asked to stop taking the medication completely. These patients will continue to be monitored for any adverse events for a period of 7 days (washout period for telmisartan) after which they will no longer be part of the trial and will return to routine care. For those who are on trial arms whose dose(s) are taken forward to stage II, they will be asked to continue on the same dose for a further 24 weeks. Since treatment is not stopped between stages I and II, some participants may receive up to a maximum of 48 weeks trial treatment before the results of the interim analysis are known. For patients recruited after the results of interim analysis are known, they will be randomised equally to the non-intervention (control) arm and the remaining telmisartan dose arm(s).

Dose modifications will be allowed in those who are randomised to a particular dose arm but do not tolerate that dose. The patient will be allowed to continue on the nearest dose tolerated. Those who show adverse effects as a result of the trial intervention or due to the HIV therapy may be withdrawn from the trial treatment. The decision to interrupt or discontinue trial therapy is at the discretion of the treating physician using their informed clinical opinion. Any changes will be documented in the CRF along with the justification for those changes. Patients who withdraw from study treatment will be asked to allow continuation of scheduled evaluations, complete an end-of-study evaluation if appropriate and be given appropriate care under medical supervision until the symptoms of any adverse event resolve or the patient's condition becomes stable. Follow-up of these patients will be continued through the trial research nurses and the lead investigator at each centre unless the participant explicitly also withdraws consent for follow-up. Data up to the time of withdrawal will be included in the analyses unless the patient explicitly states that this is not their wish.

## Patient follow-up

Apart from the dose-titration visits for participants in the 40 and 80 mg arms, follow-up visits will be designed to fit with routine hospital visits where possible. The study will also allow a 2 week window on either side of the scheduled follow-up visit date to ensure flexibility. Individual patients will be sent reminders about follow-up visits by the research nurses provided they have agreed to receive them. If any of the trial patients are lost to follow-up, contact will be attempted through the research nurse and lead investigator at each centre. Wherever possible, information on the reason for loss to follow-up will be recorded.

## Outcomes and assessments

Efficacy of trial treatments will be assessed throughout the period of the study. The primary outcome measure is a reduction in insulin resistance (as measured by HOMA-IR) in telmisartan treated arm(s) after 24 weeks of treatment in comparison with the non-intervention arm. Fasting plasma and serum samples will be collected from each participant at baseline and at follow-up visits (weeks 12, 24 and 48) and stored under appropriate conditions locally. Biochemical analyses will be carried out centrally in an accredited clinical laboratory. Fasting plasma glucose will be measured by standard clinical methods and serum insulin will be measured by an electrochemiluminescence immunoassay using a Cobas C Analyser (Roche Diagnostics, Switzerland). HOMA-IR will be calculated using the equation: (fasting serum insulin (mU/L)×fasting plasma glucose (mmol/L))/22.5. The secondary outcome measures are detailed in box 2. Serum and urine biomarker analyses and DNA extraction will be performed centrally using Human Multiplex ELISA (Millipore) on a BioPlex 200 System (BioRad) and Chemagic Magnetic Separation Module I (MSM I), respectively.
Box 2Secondary outcome measuresChange in lipid profile (total cholesterol, triglycerides, LDL-c and HDL-c) at weeks 12, 24 and 48 between telmisartan treated arm(s) and the control arm.Change in body fat redistribution as measured by MRI/MRS at 24 weeks between telmisartan treated arm(s) and control arm (See substudy).Change in plasma concentrations of biomarkers (adiponectin, lipin1, IL-6, TNF-α, resistin and hs-CRP) at 12, 24 and 48 weeks between telmisartan treated arm(s) and control arm.Change in insulin resistance, measured longitudinally at weeks 12 and 48, in telmisartan treated arm(s) in comparison with the control arm.Change in urinary biomarker levels at 12, 24 and 48 weeks between telmisartan treated arm(s) and the control arm.Difference in expected and unexpected serious adverse events between different telmisartan treated dose arm(s) and the control arm over the study follow-up.HDL-c, high density lipoprotein-cholesterol; hs-CRP, high sensitive, C reactive protein; IL-6, interleukin-6; LDL-c, low density lipoprotein-cholesterol; TNF-α, tumour necrosis factor-α.

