**Methods and analysis:**

This is a phase II, multicentre, randomised, open-labelled, dose-ranging trial of telmisartan in 336 HIV-positive individuals over a period of 48 weeks. The trial will use an adaptive design to inform the optimal dose of telmisartan. Patients will be randomised initially 1:1:1:1 to receive one of the three doses of telmisartan (20, 40 and 80 mg) or no intervention (control). An interim analysis will be performed when half of the planned maximum of 336 patients have been followed up for at least 24 weeks. The second stage of the study will depend on the results of interim analysis. The primary outcome measure is a reduction in insulin resistance (as measured by Homeostatic Model Assessment—Insulin Resistance (HOMA-IR)) in telmisartan treated arm(s) after 24 weeks of treatment in comparison with the non-intervention arm. The secondary outcome measures include changes in lipid profile; body fat redistribution (as measured by MRI); plasma and urinary levels of various biomarkers of cardiometabolic and renal health at 12, 24 and 48 weeks. Serious adverse events will be compared between different telmisartan treated dose arm(s) and the control arm.

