## Trial design

This study is a phase II, multicentre, randomised, open-labelled, dose-ranging trial of telmisartan in HIV-positive individuals over a period of 48 weeks. The sample size for the study is 336 (see Sample size calculation), but a total of 370 patients will be recruited to participate in this study to account for patient withdrawals (estimated to be 10%).

The optimal dose of telmisartan that elicits the desired response is not known; hence, an adaptive design is utilised for this study. The first stage of the study will be dose-ranging where patients will be randomised 1:1:1:1 to receive one of three doses of telmisartan (20, 40 and 80 mg) or no intervention (control). An interim analysis will be performed when half of the planned maximum of 336 patients have been followed up for at least 24 weeks. The second stage of the study will depend on the results of interim analysis, which could be one of the three outcomes listed below:
One or more active dose groups are substantially more effective than control; this will lead to a stopping of the study and the corresponding dose(s) will be taken directly into phase III.No dose shows sufficient promise at the interim analysis; this will also lead to a stopping of the study.At least one of the doses shows some improvement over control at interim analysis; this will lead to a second stage where that/these dose(s) will be followed up along with the control for a further 24 weeks (total: 48 weeks). Additional patients will also be recruited to these dose(s) and control. If at the final analysis a large enough reduction in 24 week HOMA-IR score is found, the corresponding active dose will be recommended for phase III.

In the telmisartan 40 and 80 mg arms, dose titration will be undertaken over 2−4 weeks in order to step up to the allocated dose (as per the Summary of Product Characteristics; SPC), or else the maximum tolerated dose if the target is not achieved. All assessments will be carried out at baseline and at weeks 12, 24 and 48 post-treatment with telmisartan, as well as in the control arm. For those who participate in the MRI/MRS substudy, assessment will be at baseline and 24 weeks. The study flow diagram is given in figure 1.

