### Secondary outcome analysis

Linear mixed effect models will be used to analyse secondary and mechanistic outcomes. The evaluation of beneficial and adverse biomarkers in relation to insulin resistance will be examined using the joint modelling approach^43^
^44^ accounting for informative loss to follow-up or censoring. Structural equation models^45^ will be used to assess the inter-relationship between multiple biomarkers over effect of treatment while accounting for time-varying confounders. Mechanistic outcomes such as change in body fat, liver and muscle fat distribution will be analysed using a multiple linear regression model. Differences will be considered significant at p<0.05. Differences between the groups will be estimated with 95% CIs.

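### The serious adverse event comparison is set over a follow-up window that is shorter, by design, in any dose dropped at the interim than in control

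*Protocol article*

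**What the plan says.** The Outcomes and assessments section (Box 2) lists the SAE outcome as "Difference in expected and unexpected serious adverse events between different telmisartan treated dose arm(s) and the control arm over the study follow-up". The abstract repeats the comparison without a window: "Serious adverse events will be compared between different telmisartan treated dose arm(s) and the control arm". Every other outcome in Box 2 is tied to named weeks (12, 24 or 48); the SAE outcome is not.

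The Trial interventions section says that patients on a dose not taken forward stop the drug and are monitored for a period "of 7 days (washout period for telmisartan) after which they will no longer be part of the trial". For doses that do go forward, the Trial design section says "this will lead to a second stage where that/these dose(s) will be followed up along with the control for a further 24 weeks", to 48 weeks in total, with further recruitment to those arms and control. Trial interventions caps treatment in the same way, "For each randomised patient, treatment is for a maximum period of 48 weeks", and notes that "some participants may receive up to a maximum of 48 weeks trial treatment before the results of the interim analysis are known", so early entrants to a dropped arm may lose no follow-up. Interim monitoring and analyses drops a dose whose interim statistic is negative, and expects that patients will have been recruited in the 24 weeks before data extraction.

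**The concern.** Taken together, these sections make study follow-up mean different lengths of time in different arms. In a dropped arm, the early entrants may complete 48 weeks, but later entrants are cut off at whatever week they have reached plus 7 days. Control and retained doses keep their full 48 weeks. They also gain patients randomised after the dropped dose has closed.

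More time at risk means more events. If SAEs are simply counted, or expressed as the proportion of patients affected, over this window, a dropped dose looks safer than control and than the retained doses even when the true risk is the same. Tolerability is a stated secondary objective, and Box 2 lists no other between-arm safety outcome. Losing a low dose could suggest a dose-toxicity gradient that is not there; losing a high dose could hide one that is.

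**Working it through.** **1. Reproduce the design.** Inputs from Sample size calculation and Interim monitoring and analyses: 42 patients per arm per stage, critical values 2.782 and 2.086, doses dropped below 0. The effects are √2·z(0.65) = 0.545 SD and √2·z(0.55) = 0.178 SD, as stated. Simulating the rules 1,000,000 times gives a one-sided type I error of 0.050 and a probability of 0.906 of recommending the best dose. The planned 0.05, 0.90 and 336 are reproduced.

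**2. How often the problem arises.** The same simulation gives the probability that the trial continues with at least one dose dropped. It is 0.50 under no effect and 0.27 under the design alternative (about 45% of the trials that continue).

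**3. Follow-up in a dropped arm.** Let A be the weeks needed to randomise 168/0.9 = 187 patients (10% loss), with uniform accrual. The data cut falls at D = A + 24 weeks, and the decision is taken at once. A patient entering at week t of the trial is followed for min(48, D − t + 1) weeks. Patients entering in the last 47 weeks before D lose on average 23.5 weeks each, so

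mean follow-up = 48 − (47/D) × 23.5, a relative shortfall of (47/D) × (23.5/48), or about 23/D.

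**4. Bounding accrual.** No recruitment rate or start date is given. Time frame and trial status gives a 56-month study and 293 patients recruited so far. Subtracting 48 weeks (about 11 months) leaves at most 45 months of recruitment. The slowest rate compatible with this is 293/45 = 6.5 per month. The fast end, 370 patients in 24 months, is an assumption. (That section also gives follow-up per participant as 48 months, against 48 weeks elsewhere. I used 48 weeks; the two must be reconciled.)

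**5. Effect on SAEs.** Assume the same constant rate in both arms, 10 per 100 patient-years. The risk in control over 48 weeks is 1 − exp(−0.10 × 48/52.18) = 8.8%. In the dropped arm, the same formula is averaged over the follow-up times in step 3. The last column applies both risks to the patients in one arm at the decision.

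| Accrual | D (weeks) | Mean follow-up (weeks) | % with an SAE, dropped v control | Ratio | Patients with an SAE per arm |
|---|---|---|---|---|---|
| 293 in 45 months | 148.7 | 40.6 | 7.5 v 8.8 | 0.85 | 4.1 v 4.9 (of 56) |
| 370 in 45 months | 122.7 | 39.0 | 7.2 v 8.8 | 0.82 | 4.2 v 5.1 (of 58) |
| 370 in 36 months | 103.0 | 37.3 | 6.9 v 8.8 | 0.78 | 4.2 v 5.3 (of 61) |
| 370 in 24 months | 76.6 | 33.6 | 6.2 v 8.8 | 0.70 | 4.2 v 6.0 (of 68) |

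The shortfall is thus about 15-30%, or 0.7 to 1.8 patients. An 8-week delay from data cut to decision lowers it by about 1 to 3 percentage points. The assumed SAE rate barely matters: at 5 or 20 per 100 patient-years the ratios stay within 0.01 of those shown. Raw counts would differ by more, because control goes on recruiting.

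**The case against.** The strongest reply is that the article names no metric. A difference over follow-up can be read as a rate per patient-year, and the denominator, censoring rule and choice of controls normally belong to the statistical analysis plan, which is not at hand. This largely stands: a reader might infer that a crude comparison is prescribed, and it is not. What remains is that the outcome's window is itself fixed here, and that the same article makes that window unequal.

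A reader might also infer that the bias could mislead the choice of phase III dose. The documents do not support that. A dropped dose has a negative efficacy statistic and is out; the recommendation rests on the largest efficacy statistic; and planned follow-up per patient is the same for retained doses and control.

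The effect is also small beside sampling error. With the patient numbers above, the 95% interval for the risk ratio would run from about 0.2 to between 2 and 3. That is correct, and it limits the weight of the point. But a systematic shift in a known direction should not be left in when removing it costs almost nothing.

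Two further readings go too far. The sentence "Linear mixed effect models will be used to analyse secondary and mechanistic outcomes" might be taken to apply linear mixed models to SAEs, but it is a condensed statement in a section that names several other models. The mention of expected and unexpected events reads naturally as all SAEs of both kinds, and nothing says that the two are tested separately.

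**Conclusion.** The point holds as a badly fixed outcome window. If the trial continues with some but not all doses dropped, an unadjusted comparison over study follow-up understates SAEs on a dropped dose relative to control and retained doses. The direction follows from the protocol text. The size, about 15-30% fewer patients with an SAE at equal risk, does not: it rests on uniform accrual within the bounds above, a prompt interim decision, an equal and constant SAE rate, and a crude proportion as the metric. If the whole trial stops at the interim, the article describes no longer follow-up for control and the issue does not arise. The consequence is confined to the account of tolerability across doses. The change should be made, but the trial's main conclusion does not depend on it.

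**What to change.** In Box 2, replace the open study-follow-up window with one of two definitions, and bring the abstract into line:

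- the SAE rate per patient-year from randomisation to last trial contact, with the rate ratio to control and its 95% CI; or
- the proportion with at least one SAE in a common window, such as to week 24.

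For a dropped dose, use only controls randomised while that dose was open, censored by the same calendar rule. This matters for both options. A rate per patient-year alone removes the bias only if the hazard is roughly constant. And patients who entered a dropped arm in the last 23 weeks before the decision have not reached week 24 (23/D, about 15-30% of the arm), so the week-24 proportion must allow for censoring.

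The cost is wording, in the outcome definition and the analysis plan. Randomisation, event and last-contact dates are ones the trial would hold anyway. The downside is a slightly wider interval for a dropped dose, because later controls are not used.
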